### **8.2 Univariate analysis**

The effect of the intervention on T cell characteristics (primary outcome measures) will be expressed as the difference between the respective continuous variables (ED50, T cell subsets or Th1/Th2 ratios) before and after treatment. The significance of this difference will be tested with a paired non-parametrical test (Wilcoxon ranking test). The same holds for the effect of the intervention on safety parameters and vitamin D metabolite values.

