To summarize, we would like to supplement a small cohort of RRMS patients, treated with interferon beta 1a or 1b, with a short disease course (<5 years) with high doses of vitamin D3 in an open label design. The main goal is to determine whether this dose is effective in modulating the T cell compartment. The primary outcome measure will be improvement of Treg function in proliferation suppression assays. Furthermore, specific safety issues will be assessed. Does an acute start with high doses vitamin D3 provoke side effects? Is calcium metabolism well regulated? Are serum 25(OH)D also effectively elevated in these patients using interferon beta 1a or 1b? The latter question is highly relevant, since therapy with Interferon Beta 1a and 1b specifically inhibits the superfamily of cytochrome P450 enzymes, to which the vitamin D hydroxylating enzymes also belong.

In MS, T cell regulation has been shown to be impaired. At present, disease modulating drugs in MS, like Beta Interferons, promote T cell regulation. The positive correlation between vitamin D status and T cell regulation that we observed in our previous study suggests that elevation of vitamin D status might result in promotion of T cell regulation. It is tempting to speculate that this promotion of T cell regulation might result in a subsequent amelioration of MS. Therefore, this study will be an important step towards assessment of vitamin D therapy in MS.

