## 2. OBJECTIVES

Primary Objective:

- Does vitamin D3 supplementation with a dose of 500 µg/ day for 12 weeks result in an improved regulatory T cell function (i.e. reduction of ED50 in the *in vitro* assay) in relapsing remitting MS patients treated with interferon beta?

Secondary Objective(s):

- Does vitamin D3 supplementation with a dose of 500 µg/ day for 12 weeks result in a shift of the T cell compartment from a Th1 to a Th2 response in relapsing remitting MS patients treated with interferon beta?
- Is supplementation of vitamin D3 with a dose of 500 µg/ day for 12 weeks effective in raising 25(OH)D levels above 100 nmol/L in relapsing remitting MS patients treated with interferon beta?
- Is supplementation of vitamin D3 with a dose of 500 µg/ day for 12 weeks safe and tolerable in relapsing remitting MS patients treated with interferon beta?

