## 6. METHODS

### 6.1 Study parameters/endpoints

#### 6.1.1 Main study parameter/endpoint

The main study endpoint is the function of regulatory T cells (CD4+CD25+CD127) in the T cell compartment. This will be assessed by testing their capability to inhibit CD3-driven Tresp (CD4+CD25) cell proliferation in culture.

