#### 6.1.2 Secondary study parameters/endpoints (if applicable)

Several other T cell characteristics of the T cell compartment will also be investigated. The number of regulatory T cells in the circulation, as well as the percentages of individual T helper cell subsets within the CD4+ T cell compartment will be determined by flow-cytometry.

Several parameters will be assessed to investigate the safety of vitamin D3 supplementation. These are:

- Plasma levels of total calcium, albumin and parathyroid hormone (PTH) to assess a potential decompensation of calcium metabolism.
- Plasma levels of phosphate, potassium, sodium, creatinine and urea to assess a potential decompensation of kidney function.
- Plasma levels of aspartate aminotransferase (AST), alanine aminotransferase (ALT), alkaline phosphatase (AP) to assess a potential decompensation of liver function.

The elevation of serum 25(OH)D and 1,25(OH)2D levels will be measured to assess the effectiveness of the intervention.

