## **8. STATISTICAL ANALYSIS**

### **8.1 Descriptive statistics**

All data will be analysed descriptively. The biochemical (vitamin D metabolite levels, calcium parameters, liver function tests, and kidney function tests) and immunological data (T cell subset percentages, percentage of Treg suppression) will be presented as continuous variables. No cut-off points will be used for any value. The demographical data will also be presented either as continuous or as categorical variables as appropriate. Of continuous data, medians and minimum-maximum ranges will be provided. Of categorical data, counts and corresponding percentages will be provided.

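### Section 8.2 labels T cell subsets and Th1/Th2 ratios as primary alongside ED50, contradicting the single primary endpoint set elsewhere in the protocol

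*Protocol*

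**What the plan says.** Section 8.2 reads: "T cell characteristics (primary outcome measures) will be expressed as the difference between the respective continuous variables (ED50, T cell subsets or Th1/Th2 ratios". The differences compare values from the start and the end of supplementation, with significance judged by a paired Wilcoxon test. The label in parentheses is plural and covers all three classes of variable. The section gives no order among them and no significance level.

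The rest of the protocol is narrower:

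- Section 1: "The primary outcome measure will be improvement of Treg function in proliferation suppression assays".
- Section 2, the only primary objective: whether supplementation will "result in an improved regulatory T cell function (i.e. reduction of ED50 in the" in vitro assay.
- Section 2, first secondary objective: whether it will "result in a shift of the T cell compartment from a Th1 to a Th2 response in relapsing remitting MS patients".
- Section 4.4: the sample size uses the mean and SD of ED50 and an ED50 target of 0.25, which it treats as the target for the primary endpoint.
- Section 6.1.1: "The main study endpoint is the function of regulatory T cells". ED50 is not named here.
- Section 6.1.2, under the secondary endpoints: "Several other T cell characteristics of the T cell compartment will also be investigated". Percentages of T helper subsets are among them.

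The Summary is looser. It gives the main parameter as the T cell compartment, with Treg function singled out within it.

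**The concern.** The analysis section is where a reader looks to see which test decides the trial. Here it gives primary status to variables that the objectives and endpoint sections call secondary. The study has one open-label arm, so the report will rest on before-after changes in several immune measures from the same patients. If ED50 did not change but one subset or a Th1/Th2 ratio did, the authors could cite 8.2 and report a change in a primary outcome, although the study was neither designed nor sized around that variable. Section 9.4 says that an effect on the T cell compartment would support going on to study a therapeutic effect in MS, so the label bears on a real decision.

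**Working it through.** **1. The passages side by side**

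- ED50 (Treg function): primary in sections 1, 2, 4.4 and 6.1.1, and primary in 8.2. Consistent.
- Th1/Th2 ratio: secondary objective in section 2, primary in 8.2. Contradiction.
- T cell subsets: secondary endpoint in 6.1.2, primary in 8.2. Contradiction.

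No other section says which label prevails.

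**2. What the sample size was based on**

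Inputs, all from section 4.4: mean ED50 1.0413, SD 0.5503, target 0.25, expected difference 0.7912 as printed, two-sided alpha 0.05 (1.96), power 80% (0.84). The protocol's own substitution is

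(1.96 + 0.84)² × (2 × 0.5503)² / 0.7912² = 7.84 × 1.93502 = 15.17, or about 15.

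The figure of 15 is reproduced as substituted. (The symbolic formula printed just before it has 2 × SD², which would give 7.59. That is a separate matter and does not affect this point.) Every input is an ED50 quantity. No subset or ratio enters the calculation.

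**3. False-positive rate if any one measure counted as primary success**

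Assumptions: each measure is tested at two-sided 0.05, the only level in the protocol; any one significant result counts; one variable is taken from each class in 8.2, so k = 3. Three is a minimum, because 8.2 writes both subsets and ratios in the plural.

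- Independent tests: 1 − (1 − 0.05)³ = 1 − 0.857375 = 0.1426, or about 14%.
- Exact Wilcoxon signed-rank test at n = 15: the two-sided size is 0.0479, because the test is discrete. Then 1 − (1 − 0.0479)³ ≈ 0.137.
- Simulation of that test (n = 15, 40,000 runs, three measures with equal correlation): 13.6% at correlation 0, 13.2% at 0.3, 12.5% at 0.5, 10.0% at 0.8. The protocol gives no correlations, so these four values are assumed.
- ED50 as the single primary outcome: nominal 5%, exact size 4.8%.

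**The case against.** The strongest reply is that the hierarchy is already fixed. Section 1 speaks of one primary outcome measure, section 2 has one primary objective with ED50 named, section 4.4 sizes the study on it, and section 6.1 separates main from secondary endpoints. On this view the words in parentheses in 8.2 are a slip, and the list only says for which variables a difference will be taken. This is a reasonable account of what was intended. It does not remove the conflict, because 8.2 is the protocol's analysis rule and says something else.

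Four stronger readings are tempting, and the documents do not support them:

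- A reader might infer that 8.2 makes any one measure at p < 0.05 a positive trial. It states no threshold and no success rule. The 0.05 comes from section 4.4, and the word joining the list may simply enumerate.
- A reader might infer that 8.1 replaces ED50 with another measure, since it lists "T cell subset percentages, percentage of Treg suppression". Section 8.1 is descriptive, and section 4.4 defines ED50 as the Treg/Tresp ratio that gives 50% suppression. Percentage suppression is therefore the readout behind ED50, and 8.2 names ED50 for testing.
- A reader might quote much higher error rates by counting many subsets. The protocol does not say how many there are. The subsets are percentages within one CD4+ compartment, so independence is also doubtful.
- A reader might fault the lack of a multiplicity method. That can be left to a statistical analysis plan, which is not shown here.

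It is also fair to say that section 6.2 calls this a pilot and section 9.4 expects no direct therapeutic effect, so familywise error matters less than in a confirmatory trial. That lowers the stakes. It does not make two conflicting definitions of the primary outcome acceptable.

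**Conclusion.** The point holds as a contradiction within the protocol. It rests on the text alone and needs no assumption. What it changes is which results may be reported as primary in an open-label, single-arm study.

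The error-rate figures are conditional. If any one of three measures were allowed to establish the primary result at two-sided 0.05, the false-positive chance would be about 14% under independence and about 10% at an assumed correlation of 0.8, against 5% for ED50 alone. They show what the wording leaves open; they are not the error rate of a rule the protocol has adopted.

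An unseen statistical analysis plan does not settle the matter. Its author would have to choose between 8.2 and sections 1, 2, 4.4 and 6.1, and in an open-label study that choice could be made after results are known. The wording should be corrected before the data are analysed.

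**What to change.** Replace the primary label in 8.2 with wording such as:

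> The single primary outcome is the change in ED50 from baseline to week 12, tested with the paired Wilcoxon test at two-sided 0.05. T cell subsets and Th1/Th2 ratios are secondary; their p-values are unadjusted and cannot establish the primary objective.

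Name ED50 in 6.1.1 as the measure of Treg function, and bring the Summary's description of the main parameter into line. Section 8.1 needs no change.

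The cost is wording only: no added patients, visits or assays. The trial gives up the option of claiming primary success on a subset or ratio result.

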### **8.3 Multivariate analysis**

No multivariate analysis will be performed.

## **9. ETHICAL CONSIDERATIONS**

### **9.1 Regulation statement**

This study will be conducted according to the principles of the Declaration of Helsinki (version DoH/Oct2008, as accorded by the 59th WMA general assembly in Seoul, October 2008) and in accordance with the Dutch Medical Research Involving Human Subjects Act (WMO).

### **9.2 Recruitment and consent**

The patients will be primarily included from the population which were included for the study 'Vitamin D and the T cell compartment in multiple sclerosis' (NL 22666.096.07). Those patients all agreed to be approached for further studies. Additionally, patients from outside this cohort matching the inclusion criteria will be approached. Patients who meet the inclusion criteria will be contacted by a research nurse. When interested, a patient brochure will be send. In this brochure, telephone numbers and e-mail addresses of the researcher and independent physician are provided. If the patient agrees to take part in the study, and appointment will be made to further check the inclusion criteria, answer eventual questions, and to sign the informed consent form.

### **9.3 Objection by minors or incapacitated subjects (if applicable)**

No minors and/or incapacitated adults will be included in this study.

### **9.4 Benefits and risks assessment, group relatedness**

Several safety studies provided evidence that supplementation of MS patients with high dose vitamin D is safe (section 5.3). Nevertheless, patients have to take the Vigantol® each day, which requires both time and commitment from our patients. Additionally, patients have to donate blood 6 times. This is as less often as possible; safety controls will be performed by assessing the serum calcium levels. The risks of a blood donation are a temporary vasovagal reaction or a local haematoma at the puncture spot.

There is at present no direct therapeutic effect of this regimen to be expected in participants. However, an effect of this intervention on the T cell compartment would provide an essential argument to investigate a therapeutic effect of vitamin D supplementation on MS.

### 9.5 Compensation for injury

The sponsor/investigator has a liability insurance which is in accordance with article 7, subsection 6 of the WMO. The insurance company is 'Vereniging Voor Arts en Auto' and the polis number 1150888 ('Orbis Medisch en zorgconcern').

The sponsor (also) has an insurance which is in accordance with the legal requirements in the Netherlands (Article 7 WMO and the Measure regarding Compulsory Insurance for Clinical Research in Humans of 23th June 2003). The insurance company is MediRisk B.A. ([name]). The polis is on the name of 'Orbis Medisch en Zorgconcern' and has the number MR017/020924/WMO. This insurance provides cover for damage to research subjects through injury or death caused by the study.

1. € 450.000,-- (i.e. four hundred and fifty thousand Euro) for death or injury for each subject who participates in the Research;
2. € 3.500.000,-- (i.e. three million five hundred thousand Euro) for death or injury for all subjects who participate in the Research;
3. € 5.000.000,-- (i.e. five million Euro) for the total damage incurred by the organisation for all damage disclosed by scientific research for the Sponsor as 'verrichter' in the meaning of said Act in each year of insurance coverage.

The insurance applies to the damage that becomes apparent during the study or within 4 years after the end of the study.

### 9.6 Incentives (if applicable)

Subject will receive no incentives for participating in the study. Travel costs will be compensated with the standard tariff of € 0.19 /km as measured by an electronic route planner.

## **10. ADMINISTRATIVE ASPECTS AND PUBLICATION**

### **10.1 Handling and storage of data and documents**

Data will be stored for each patient in one single master-file. After completing the informed consent form, patient will receive a code under which their data will be stored in the master file. Patients will receive a code at order of inclusion. Coding will start at 201, 202, 203, etc. Only the principal investigator has access to the informed consent forms and key to the code. Material which is stored (serum, plasma) will be labelled with the research code of the patient and will be destroyed at the end of the study.

### **10.2 Amendments**

A 'substantial amendment' is defined as an amendment to the terms of the METC application, or to the protocol or any other supporting documentation, that is likely to affect to a significant degree:

- the safety or physical or mental integrity of the subjects of the study;
- the scientific value of the study;
- the conduct or management of the study; or
- the quality or safety of any intervention used in the study.

All substantial amendments will be notified to the METC.

Non-substantial amendments will not be notified to the accredited METC, but will be recorded and filed by the sponsor.

### **10.3 Annual progress report**

The sponsor/investigator will submit a summary of the progress of the trial to the accredited METC once a year. Information will be provided on the date of inclusion of the first subject, numbers of subjects included and numbers of subjects that have completed the trial, serious adverse events/ serious adverse reactions, other problems, and amendments.

### **10.4 End of study report**

The investigator will notify the accredited METC of the end of the study within a period of 8 weeks. The end of the study is defined as the last biochemical test performed on the last patients material.

In case the study is ended prematurely, the investigator will notify the accredited METC, including the reasons for the premature termination.

Within one year after the end of the study, the investigator/sponsor will submit a final study report with the results of the study, including any publications/abstracts of the study, to the accredited METC.

#### **10.5 Public disclosure and publication policy**

The results of this study, regardless their nature, will be published in a scientific paper, and/ or be presented at a scientific congress.

